# Early skin contact combined with mother’s breastfeeding to shorten the process of premature infants ≤ 30 weeks of gestation to achieve full oral feeding: the study protocol of a randomized controlled trial

**DOI:** 10.1186/s13063-021-05605-x

**Published:** 2021-09-17

**Keywords:** Skin contact, Breastfeeding, Preterm infants, Full oral feeding, Randomized controlled trial

## Abstract

**Background:**

Most hospitalized preterm infants experience difficulties in transitioning from tube feeding to full oral feeding. Interventions to promote full oral feeding in preterm infants in the neonatal intensive care unit (NICU) are limited to pacifier use or bottle-feeding exercises. Skin contact has been shown to be beneficial to start and maintain lactation and provide preterm infants with the opportunity to suck on the mother’s breast, which may promote further development of the preterm infant’s suckling patterns. The objective of this study is to compare and evaluate the effects of skin contact combined with breastfeeding (suck on the mother’s empty breast) as compared to the routine pacifier suckling training model in achieving full oral feeding for infants whose gestational age are ≤ 30 weeks.

**Methods:**

This is a single-center, randomized controlled clinical trial conducted in the NICU and designed according to the SPIRIT Statement. The subjects included in the study are premature infants born between April 2020 and July 2021 with a gestational age of ≤30 weeks, birth weight of <1500 g, admission age of <72 h, and absence of congenital malformations. Those with oxygenation indices of >40 and those born to mothers with poor verbal communication skills will be excluded. A sample of 148 infants is needed. The infants will be randomized to the intervention (skin contact combined with mother’s breastfeeding model) or control group (routine pacifier sucking training model). The primary outcome is the time required to achieve full oral feeding. The secondary outcomes are the breastfeeding abilities of preterm infants as assessed by the Preterm Infant Breastfeeding Behavior Scale (PIBBS), breastfeeding rates at 3 and 6 months corrected gestational age, complication rates, duration of oxygen requirement, days of hospital stay, and satisfaction of parents.

**Discussion:**

This paper describes the first single-center, open-label, randomized clinical trial on this topic and will provide crucial information to support the implementation of skin contact combined with the breastfeeding model in the NICU setting.

**Trial registration:**

ClinicalTrials.gov NCT 04283682. Registered on 8 February 2020.

**Supplementary Information:**

The online version contains supplementary material available at 10.1186/s13063-021-05605-x.

## Background

Oral feeding is a complex sensory motor process which is affected by many factors. The brain of the preterm infant is not fully developed and thus neural development is incomplete. Oral feeding is difficult due to decreased abilities in sucking and swallowing, discordant breathing, and immature behavior state organizational capabilities [1, 2]. Studies report that 80% of preterm infants experience oral feeding difficulties with the degree of feeding difficulty related to gestational age [3, 4]. Although sucking and swallowing appears at 28 weeks of gestation, full coordination of sucking, swallowing, and breathing should be achieved at between 32 and 34 weeks’ gestation, which means that preterm infants less than 32 weeks of gestation are unable to feed orally by breast or bottle [4–9].

During neonatal intensive care unit (NICU) admission, preterm infants often require nasogastric or orogastric tube feeding before progressing to oral feeds once they are mature enough to do so [10]. Preterm infants’ readiness for full oral feeding is related to gestational age. According to research data on preterm infants at different gestational ages, full oral feeding was achieved at 10–36 days of life [11–14]. Establishment of full oral feeding in preterm infants is an important factor affecting the length of hospital stay and is also one of the criteria considered for discharge from the NICU [15–18].

Studies have shown that preterm infants can achieve full oral feeding before 34 weeks’ gestation through external stimulation (e.g., pacifier, lullabies, music, the smell of breast milk, kangaroo care) [19]. Oral feeding training can improve the experience and maturity of sucking [4, 20–23]. Preterm infants show obvious signs of rooting, grasping, and repeated short sucking at 29 weeks’ gestation and occasionally long sucking and repeated swallowing at 31 weeks’ gestation. Regular training in non-nutritive sucking can allow the preterm infant to gain experience in feeding, promote the formation of mature sucking, and contribute to the development of feeding skills [2, 4]. Nyquist et al. found that babies can root, latch, and effectively contain the areola at 28 weeks of gestation when they come into contact with their mother’s breasts [24]. There was no correlation between the rooting behavior, sucking, and gestational age. After 30 weeks’ gestation, preterm infants can exhibit nutritive sucking. Repeated bursts of more than 10 sucks and maximum bursts of more than 30 sucks are observed at 32 weeks [24].

Non-nutritive sucking by sucking the mother’s “empty” breast is more conducive to promoting the development and maturity of sucking than using a pacifier. This sucking is completed at the source of nutrition without affecting nutrient intake. When sucking the “empty” breast, the baby showed that the nipple was tightly locked and fixed on the nipple. Time spent in active sucking, sucking burst, and swallowing were all longer and feeding behavior was more mature [25]. Skin-to-skin contact (SSC) is a maternal and infant practice recommended by the World Health Organization (WHO). It has been proven that SSC plays an important role in both infants and mothers [26]. The sleep or wakefulness behavior of infants receiving SSC is more organized, and they have more time in quiet sleep and in the alert awake state [27, 28]. SSC contributes to the development of the infant’s nervous system [28–30], and it has been reported that infants receiving SSC have shorter hospital stays and lower infection severity [31, 32]. Infants who received SSC had higher intelligence and better psychomotor development at 12 months corrected gestational age [30]. From the breastfeeding perspective, SSC can improve the production of breast milk, help establish breastfeeding, prolong the duration of breastfeeding, enhance the willingness to breastfeed [33–35], and help to reduce stress in new mothers [35].

In the process, the mother expresses breast milk prior to tube feeding and tube feeding is combined with skin-to-skin contact. The mother manually drips the breast milk onto the baby’s lips, and the baby tastes and becomes familiar with breast milk while being tube-fed. Non-nutritive sucking on the breast is conducive to the transition from tube feeding to breastfeeding, which is in turn conducive to breastfeeding [36]. As the infant matures, the infant will naturally approach the breast during SSC, which triggers instinctive breastfeeding behavior, promotes the coordination of sucking and swallowing, starts the first nutritive sucking earlier, and improves the duration of sucking, so as to satisfy the infant’s instinctive desire to suck.

At present, many NICUs promote oral feeding of preterm infants mainly by non-nutritive sucking and tube feeding, and the outcome indicator is predominantly successful establishment of bottle feeding. Studies on skin contact in stable preterm infants mainly focus on temperature management, weight gain, breast milk secretion, and parental satisfaction. Family-centered care focuses more on the interaction between parents and preterm infants during hospitalization and while in transitional care before discharge. In the early stages of establishing feeds, the lack of participation of lactating mothers and the loss of the most natural active feeding support led to the prolonging of the feeding process and of hospital stay.

Therefore, the primary objective of this study is to explore whether empty breast sucking combined with skin contact can shorten the process of full oral feeding of preterm infants with gestational age ≤ 30 weeks.

## Methods/design

### Study setting and design

We will conduct a randomized, open-label clinical trial in the NICU at the Children’s Hospital of Fudan University (CHFU) in Shanghai, China. CHFU has a capacity of 1000 beds with a large neonatal center consisting of 80 NICU beds. Patients requiring admission to the NICU are those who are especially critical, approximately 2200 annually. These patients are transported from all regions of the country, with a higher proportion from the Yangtze River Delta region. More than half of these patients are preterm with approximately 500 very low birth weight infants admitted to the CHFU annually. This protocol refers to the SPIRIT 2013 Statement (Standard Protocol Items: Recommendations for Interventional Trials). A SPIRIT checklist is seen in Additional file 1. The procedures of the trial are presented in Fig. 1.

**Fig. 1 Fig1:**
[figure not shown]
The procedure of the trial

### Study subjects and recruitment

Preterm infants will be treated in the NICU at the CHFU meeting the following inclusion criteria:
Gestational age ≤ 30 weeksBirth weight < 1500gAdmission age < 72hNo congenital malformations

Exclusion criteria:
Oxygenation index (OI = 100 × mean airway pressure (MAP) × FiO_2_/PaO_2_) > 40Mother unable to communicate adequatelyTwins or multiple births

Dropout criteria:
Death or withdrawing treatment during hospitalizingMothers are unable to provide empty breast sucking or skin contact due to illness or other reasonsPremature infants cannot receive oral feeding due to disease

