### Interventions

#### The control group

After withdrawing mechanical ventilation, before each feed, a pacifier is used for 5–10 min of non-nutritive sucking. Feeds are given with a special bottle designed for preterm infants. Body weight is measured before the first oral feeding is given. When oral feeding is commenced, the infant’s mother will be informed by telephone that this has started. At this point, the HAD questionnaire is sent to the mother for a second time for completion within 24 h. According to the oral feeding schedule, the frequency of oral feeds is gradually increased. Full oral feeding is considered established when the daily amount of oral feeding milk reaches 75% of the required volume, no gavage feeding is needed for 48 h, and the daily body weight increases by 10–15g/kg/day. At this time, the infant is weighed, the mother is informed by phone, and the HAD questionnaire is sent to the mother for the third time for completion within 24 h. The weight will be measured again on the day of discharge, and parental satisfaction will be assessed by EMPATHIC-N [38]. On discharge, the HAD questionnaire was sent to the mother for the fourth time for completion within 24 h. And the PIBBS scale will be used to evaluate the breastfeeding behavior of preterm infants on discharge day. The research team members will organize and enter data on the infant’s clinical course in the hospital, and a second-team member will be responsible for verifying the data collection and entry. After discharge, the rate and mode of breastfeeding will be followed up by breastfeeding education nurses at 3 and 6 months corrected gestational age.

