#### The intervention group

After the withdrawal of mechanical ventilation, the infant will be assessed for 12 to 24 h and participants in the intervention group would receive a combination of skin-to-skin contact and breastfeeding. When the infant’s condition is stable, the mother will be invited to enter the NICU, and the HAD questionnaire will be sent to the mother for the second time for completion within 24 h. Before SSC, the mother pumps and expresses breast milk for about 15 min. Nurses assist the SSC process and carry out empty breast sucking (suck on empty breast) training for 5 to 10 min. In case of non-skin contact, a pacifier shall be used for sucking before tube feeding. SSC will be carried out at least once a day for 1 h, and monitoring should be done at the same time. The infant will be fed by a nasogastric tube. At 32 weeks’ gestation, attempts will be made to feed the infant by the bottle, using bottles specially designed for preterm infants. Before feeding, non-nutritive sucking will be conducted with a pacifier for 5 to 10 min. The number of oral feeding attempts will be gradually increased according to the oral feeding schedule. Achievement of full oral feeding is achieved when the daily amount of oral feeding milk reaches 75% of the required volume, no gavage feeding is needed for 48 h, and the daily body weight increases by 10–15g/kg/day. At this point, the infant is weighed, SSC is ceased, and the HAD questionnaire is sent to the mother for the third time for completion within 24 h. The weight will be measured on this day. On the day of discharge, the infant is weighed, and parental satisfaction will be assessed by EMPATHIC-N [38]. And the PIBBS scale will be used to evaluate the breastfeeding behavior of preterm infants on discharge day. The HAD questionnaire is sent to the mother for the fourth time at this time for completion within 24 h. Research team members will complete the organization and entry of the infant’s clinical course in the hospital, and a second-team member will be responsible for verifying the collection and entry of the information. After discharge, the rate and mode of breastfeeding will be followed up by breastfeeding education nurses at 3 and 6 months corrected gestational age.

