### Sample size

Sample size calculation is performed based on the primary outcome that is the time to achieve full oral feeding. The average days to achieve full oral feeding was 14 days with a standard deviation of 7 days in the control group according to the previous study. The time for the intervention group to achieve full oral feeding was 4 days shorter than that of the control group [48]. The sample size of 66 in each group could achieve 90% power to detect a difference of 4.0 between the groups with estimated group standard deviations of 7.0 and with a significance level (alpha) of 0.05. At least 74 subjects will be recruited in each group considering a 10% drop rate. Sample size calculation was performed by Power Analysis & Sample Size ® software version 16.0 (NCSS, LLC. USA).

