### Randomization

The subjects will be randomly allocated to the intervention group or the control group by block randomization method with a block size of 4 and allocation of 1:1. The randomization will be done by SAS version 9.4 (SAS Institute, Inc). A sequence of subjects’ IDs and intervention allocations will be generated, which by creating a random variable and ordering on that variable. The allocation sequence will be concealed by the statistician and placed in sequentially numbered, opaque, sealed, and stapled envelopes. After signing the informed consent from parents, the study investigators will open the envelopes in consecutive orders and randomly assign the subjects to the intervention group or the control group according to the allocation scheme in the envelope. The staff who analyze the outcome is unaware of the allocation of subjects.

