### Statistical analyses

All analyses will be performed using SPSS 22.0 (IBM SPSS Statistics, IBM Corporation, Chicago, IL). The two-tailed significance level will be set to *P* < 0.05. An intention-to-treat (ITT) analysis will be used for the outcomes. For primary outcome analyses, the generalized linear model (GLM) will be used to test the difference of the time to achieve full oral feeding (days) between the groups, and the estimated means and two-sided 95% confidence intervals (CI) will be derived. The clinical factors including gestational age, sex, birth weight, admission age, oxygenation indices (OI), etc. will be adjusted in the covariate-adjusted analysis of the primary outcome by the GLM model. If any subjects dropped off from the primary endpoint, modified ITT analysis will be performed by using the available subjects.

All secondary outcomes will be analyzed by GLM. Binary secondary outcomes will be summarized as absolute numbers and percentages, and the difference and its 95% CIs between the two groups will be estimated. The continuous outcome will be presented as means and standard deviations (SD) and be analyzed with the same strategy and method with that is used for the primary outcome.

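### A dropout criterion that in practice only the intervention arm can meet would let non-adherent infants leave the primary analysis, in conflict with the stated ITT

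*Protocol article*

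**What the plan says.** All references are to the protocol article.

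- **Study subjects and recruitment** gives three dropout criteria. One is death or withdrawn treatment, and one is disease that prevents oral feeding. The third covers mothers who are "unable to provide empty breast sucking or skin contact due to illness or other" reasons.
- **The intervention group**: after ventilation is withdrawn and the infant has been assessed for 12 to 24 h, "participants in the intervention group would receive a combination of skin-to-skin contact and breastfeeding".
- **The control group**: "before each feed, a pacifier is used for 5–10 min of non-nutritive sucking". The mother is contacted by telephone, and neither skin contact nor empty-breast sucking is asked of her.
- **Randomization**: "After signing the informed consent from parents, the study investigators will open the envelopes in consecutive orders". Allocation therefore comes before any attempt at skin contact.
- **Study setting and design**: "We will conduct a randomized, open-label clinical trial in the NICU".
- **Statistical analyses**: "An intention-to-treat (ITT) analysis will be used for the outcomes". The same paragraph adds: "If any subjects dropped off from the primary endpoint, modified ITT analysis will be performed by using the available subjects".
- **Sample size**: "The sample size of 66 in each group could achieve 90% power to detect a difference of 4.0 between the groups", raised to 74 per group for a 10% drop rate.

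**The concern.** A mother who cannot deliver the allocated procedure is a case of non-adherence, and ITT exists to keep such cases in the comparison. Here the plan calls it a study dropout. The criterion names no arm, but a control mother is never asked for the procedure, so nothing would trigger or record it for her. The wording is open-ended because it extends to unspecified other reasons, and in an open-label trial the people applying it know the allocation.

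Nothing in this criterion makes the endpoint missing. Enteral nutrition and weight are recorded daily until discharge (Management before procedure), and feeding is in the nursing documents (Data collection). The other two criteria differ, because death, withdrawn treatment or inability to feed orally can prevent the endpoint from occurring.

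If these infants are left out, the primary comparison sets adherent intervention infants against all control infants, including control infants whose mothers would also have been unable to take part. The balance created by randomisation is lost for the primary outcome.

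**Working it through.** **1. The plan's own figure.** Inputs from Sample size and Statistical analyses: difference 4.0 days, SD 7.0, two-sided alpha 0.05, power 90%. The two-sample t test (noncentral t) gives 89.9% power at 65 per arm and 90.3% at 66, so 66 reproduces. Inflation: 66 / 0.9 = 73.3, rounded up to 74 per arm, 148 in total. There is no arithmetic error. Dividing by 0.9 fits a plan in which dropouts are not among the 66 analysed.

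**2. Assumptions, not in the documents.** A share p of the intervention arm meets the criterion and is removed. Those infants gain nothing from the allocation, and their interval from first to full oral feeding is d days longer than that of the infants kept. The control arm has the same mix but loses nobody. The SD stays at 7. I take p = 5% to 10%, because the plan allows 10% for all dropout together, and d = 0 to 7 days (0 to 1 SD).

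**3. Bias formula.** With true benefit D in infants who receive the procedure:

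- difference with everyone kept (ITT) = D × (1 − p)
- difference after removal = D + p × d
- overstatement = p × (D + d)

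**4. No true effect (D = 0).** The bias is p × d. Type I error comes from the noncentral t with 74 × (1 − p) against 74 infants and standard error 7 × √(1/n₁ + 1/74).

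| p | d (days) | bias (days) | two-sided type I error |
|---|---|---|---|
| 5% | 0 | 0 | 5.0% |
| 5% | 3.5 | 0.05 × 3.5 = 0.18 | 5.3% |
| 5% | 7 | 0.05 × 7 = 0.35 | 6.0% |
| 10% | 0 | 0 | 5.0% |
| 10% | 3.5 | 0.10 × 3.5 = 0.35 | 6.0% |
| 10% | 7 | 0.10 × 7 = 0.70 | 9.0% |

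For the last row, n₁ = 66.6, the standard error is 1.18 days and the shift is 0.70 / 1.18 = 0.59 standard errors. If the removed infants were instead 2 days faster, p = 10% gives 0.10 × (−2) = −0.2 days, which is against the intervention.

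**5. True effect of 4 days, equal prognosis (D = 4, d = 0).**

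- p = 5%: ITT 4 × 0.95 = 3.8 days, after removal 4.0, overstated by 0.2.
- p = 10%: ITT 4 × 0.90 = 3.6 days, after removal 4.0, overstated by 0.4.

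**6. Power if everyone is kept.** With 74 analysed per arm and SD 7, power is 90.7% for 3.8 days and 87.4% for 3.6 days.

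**The case against.** The strongest reply is that the article never says these infants are removed. The available-subjects rule is triggered by loss of the primary endpoint, not by meeting a dropout criterion, and an infant whose mother cannot attend may still have the endpoint and so be available. That reading is possible, but it is stated nowhere. It also leaves unexplained why non-delivery is listed as dropout and why the sample size is inflated for dropout. The full protocol or analysis plan may settle the matter, but the article does state both rules, and as stated they do not fit together.

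The intervention section provides a pacifier for occasions without skin contact, so a single missed session need not make a dropout. This stands. It narrows the criterion to mothers who cannot deliver the procedure more generally.

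The analysts are said to be unaware of allocation. That does not help, because the dropout decision is made before the data reach them.

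A reader might infer three stronger things that the documents do not support:

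- **That the bias certainly favours the intervention.** Nothing in the article links maternal illness or absence to a longer feeding interval.
- **That infants too unstable for contact are removed from one arm.** This criterion concerns mothers. The infant-side criterion, disease preventing oral feeding, applies to both arms.
- **That the type I error could exceed 20%.** That takes p = 20% with d = 7 (bias 1.4 days, type I error 20.7%), which is twice the plan's whole dropout allowance from this one reason, combined with a difference of a full SD.

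**Conclusion.** The point holds in a bounded form. The criterion operates in one arm in practice, acts after open-label allocation, and with the available-subjects rule and the 10% allowance most naturally means that non-adherent intervention infants leave the primary analysis. That conflicts with the ITT statement.

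The distortion would be expected to favour the intervention if the procedure works or if the removed infants are slower feeders. Under no effect it is nil with equal prognosis and reverses if they are faster. For p = 5% to 10% and d = 0 to 7 days, the bias under no effect is at most 0.7 days, or 0.7 / 4 = 17.5% of the target difference, with a type I error of at most about 9.0%. Both p and d are assumptions. The conflict between the passages does not depend on them, and it should be resolved before the primary analysis.

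**What to change.** 1. State that a mother's inability to provide the procedure means non-receipt of the procedure only and is not study dropout. The bullet need not be deleted. Record the reason.
2. Follow these infants to full oral feeding and discharge, and include them in the primary analysis in their randomised arm.
3. Keep the available-subjects rule, but limit it to infants whose endpoint truly cannot be observed, for example because of death, withdrawn treatment or never being able to feed orally. Report their numbers by arm. Striking the rule altogether would leave these infants without any provision.
4. Make any per-protocol analysis supportive only.

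**Cost.** No new data are needed, because feeding and weight are already recorded until discharge. The price is dilution: if these infants gain nothing, power with 74 analysed per arm is about 91% at p = 5% and 87% at p = 10%. It would be lower if other infants also lack the endpoint. This is the power that the ITT comparison has under these assumptions, and it is no reason to exclude the infants.
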